#### Contents of motivational counseling

The intervention will focus on individual goal setting and self-efficacy, where participants describe their everyday life in terms of sitting time and decide how to reduce it, how to overcome barriers and what behavioral goal, in terms of reducing sitting time, they aim for [39]. Motivational counseling techniques will be used [38].

First, the project staff will introduce the patients to the possible benefits of reducing their daily sitting time. Secondly, they will ask the patients to describe their typical day in order to identify resources and barriers for reduction of daily sitting time and to discuss possible solutions to overcome those barriers and to use the available resources. Thirdly, the patients will set their own behavioral goals for reduction of daily sitting time using a ‘catalogue of ideas’, which contains proposals to reduce and create breaks in sitting time. Specific proposals to reduce daily sitting time are, for example, to stand up during phone conversations or TV-watching, to get up frequently to go to the printer, to get up and walk around at least once every half hour, to get up to change the TV channel, to make only one cup of coffee at a time. During the second and third motivational counseling sessions patients’ own behavioral goals will be evaluated, new goals will be set and possible solution strategies will be discussed. The patients’ motivation and confidence in their own ability to change will be in focus during the last two sessions.

In addition to the motivational counseling, four key messages or themes including ideas and suggestions for reduction of sitting time (that are written in booklets) will be handed to the patients at each session. The 4 key messages are: 1) reduce daily TV-viewing, 2) substitute sitting with standing when possible - at work and/or at home, 3) break up prolonged sitting - by standing up frequently and 4) maximum 30 minutes of sitting per episode [40]. All intervention group participants will fill out a questionnaire on process, side-effects, quality and impact of the intervention when the intervention program is completed.2)Individual SMS reminders

Based on the patients’ own individual behavioral goals the patients will decide how many weekly SMS reminders they want to receive during the 16-week intervention period and at what time of the day. Examples of SMSs are shown below:Hello X. Stand up and allow gravity to assist you to digest your lunch. Bonus: you burn more energy when you standHi X. Regard vacuum cleaning as a free fitness hour. Make a playlist, put music in your ears and do not stop until the list and the cleaning are doneHi X. You have some truly privileged colleagues who will be able to see you stand up by your table this afternoon. Show them how to do it, and they might follow your good exampleHey X. Put the remote control next to the TV if you turn on the television today. Every time you change the channel your entire body gets some exercise

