#### Control group

The control group will be encouraged to maintain their usual lifestyle during the 16-week intervention period. When the last follow-up examination is completed they will be offered the opportunity to join an information session (in groups) about the principles of the intervention.

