### Data collection

Measurements will be repeated 4 times during the 22 months: 1) at baseline; 2) at the end of the intervention (16 weeks after intervention start); 3) 6 months post intervention and finally (4) 18 months post intervention (Table 1). At each time point patients will complete self-reported questionnaires regarding demographics, lifestyle, sitting time at work and in leisure time, physical activity, physical function, pain, fatigue, health-related quality of life (HR-QoL) and general self-efficacy. Blood pressure, height, weight, waist circumference will be measured subsequently. Blood samples will be drawn and stored at the Department of Diagnostics, Division of Clinical Biochemistry, Glostrup Hospital, University of Copenhagen.

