**Table 1 Tab1:** **Collection of patient characteristics and outcome measures**

	**Screening**	**Baseline**	**4 months by end of intervention**	**6 months post intervention**	**18 months post intervention**
Background					
Marital status		X			
Age		X			
Country of birth		X			
Cohabiting		X			
Level of education		X			
Employment status		X			
Annual household income		X			
Health-related issues					
Smoking		X	X	X	X
Alcohol consumption		X	X	X	X
Medical history					
Diagnosed with RA	X				
Actual treatment for RA		X	X	X	X
DAS 28		X	X	X	X
IgM-Rheumatoid Factor		X			
ACPA		X			
Co-morbidities					
Diabetes		X	X	X	X
Hypertension		X	X	X	X
Heart attack		X	X	X	X
Stroke		X	X	X	X
COPD		X	X	X	X
Cancer		X	X	X	X
Osteoarthritis		X	X	X	X
Osteoporosis		X	X	X	X
Asthma		X	X	X	X
Depression		X	X	X	X
Medicine					
Consumption of painkillers		X	X	X	X
Serum lipids					
Total cholesterol		X	X	X	X
High-density lipoprotein cholesterol (HDL)		X	X	X	X
Triglycerides		X	X	X	X
Low-density lipoprotein cholesterol (LDL)		X	X	X	X
Very low-density lipoprotein cholesterol (VLDL)		X	X	X	X
C-reactive protein (CRP)		X	X	X	X
HbA1c		X	X	X	X
Anthropometric measures					
Weight		X	X	X	X
Height		X			
Blood pressure		X	X	X	X
Waist circumference		X	X	X	X
Body mass index; BMI		X	X	X	X
Daily sitting time					
Measured total sitting time in hours and minutes (measured by ActivePAL®)		X	X	X	X
Self-reported daily sitting time (measured by physical activity - PAS, item 4)	X	X	X	X	X
Questionnaires (self-reported)					
Physical Activity Scale - PAS	X	X	X	X	X
Fatigue - MFI		X	X	X	X
Pain - VAS		X	X	X	X
Physical function - HAQ	X	X	X	X	X
HR-QoL - SF-36		X	X	X	X
HR-QoL - EuroQol/EQ-5D		X	X	X	X
General Self-Efficacy Scale - GSES		X	X	X	X
Specific questions on sedentary behavior at work and leisure		X	X	X	X

Table 1 shows the procedure of collecting data (objectively measured and self-reported) about the trial patients from baseline to 18 months follow-up.

Anti-CCP, anti-citrullinated peptide antibody; DAS 28: Disease Activity Score Based on 28 Joints; GSES: The General Self-Efficacy Scale; HAQ: Health Assessment Questionnaire; HR-QoL, health-related quality of life; MFI: Multi-dimensional Fatigue Inventory; RA: rheumatoid arthritis; SF-36: The Short Form [36] Health Survey.

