Baseline demographic characteristics of patients are collected (electronically) via a self-report questionnaire (using tablets). Two occupational therapists will attach the ActivPAL® monitor [41] and instruct patients in how to wear the monitor 24 hours per day for 7 days. All ActivPAL® will be coded to start from midnight following the first day of application. One week (7 days) after baseline measurements the patient will return to the hospital for removal of the ActivPAL®. At the same time the patient will be informed by the Project Leader (TT) about the group allocation. One week after each of the follow-up measurements the patients will return the ActivPAL® in a closed envelope. During each 7 day-period with ActivPal® the patients fill a diary about their resting time and sleeping time in order to isolate their sitting time from sleeping time. At each medical visit to the outpatient clinic, the treating rheumatologist registers information in DANBIO including data regarding disease characteristics (for example, patient-reported outcomes, disease activity, functional status, disease course) and medical treatment [37]. Patients will not be blinded to the intervention; however, all assessors will be blinded for the two participating groups.

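### Side-effect reports are collected only in the intervention arm, so event-type complaints have no control comparator

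*Protocol article*

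**What the plan says.** Under Contents of motivational counseling, the protocol article states: "All intervention group participants will fill out a questionnaire on process, side-effects, quality and impact of the intervention". The timing follows directly: "when the intervention program is completed". So the side-effect items sit in a programme evaluation given once, in one arm.

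The Control group section says "The control group will be encouraged to maintain their usual lifestyle during the 16-week intervention period" and adds an information session offered after the last follow-up. It describes no side-effect enquiry.

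The questionnaires for both arms are listed under Data collection: "At each time point patients will complete self-reported questionnaires regarding demographics, lifestyle, sitting time at work and in leisure time", and then "physical activity, physical function, pain, fatigue, health-related quality of life (HR-QoL) and general self-efficacy". Table 1 schedules pain VAS, MFI, HAQ, SF-36, EQ-5D, DAS 28, CRP, self-reported comorbidities and "Consumption of painkillers" at baseline and all three follow-ups, with no restriction by arm. None of these lists has an item on side-effects, falls or injuries.

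Two further sources are not tied to trial visits. At outpatient clinic visits "the treating rheumatologist registers information in DANBIO including data regarding disease characteristics (for example, patient-reported outcomes, disease activity, functional status, disease course" and treatment. Cost data and Cost analysis add registry data on hospital care, primary care and prescriptions for both arms.

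**The concern.** The programme asks patients to stand more, rise often and break up sitting. The complaints this might provoke in RA, such as sore or swollen joints, a flare or a fall, also occur without it: Background and rationale describes RA as running in flares with swelling, stiffness and intense pain. If only treated patients are asked, the count mixes programme effects with the ordinary course of the disease, and nothing in the plan separates the two.

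Two features make this worse. Patients are not blinded, so asking only treated patients about side-effects of the intervention invites them to attribute a routine flare to it. The article also looks ahead to use in clinical practice if results are positive, and to transfer to other patients with limited mobility. A side-effect count without a comparator supports neither reassurance nor alarm for that purpose.

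**Working it through.** **1. What is asked, of whom, and when.**

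| Information | Intervention | Control | When |
|---|---|---|---|
| Side-effect items | Yes | None described | Once, at programme end |
| Pain VAS, MFI, HAQ, SF-36, EQ-5D | Yes | Yes | Baseline and three follow-ups |
| DAS 28, CRP, painkiller use, comorbidities | Yes | Yes | Baseline and three follow-ups |
| DANBIO clinical entries | Yes | Yes | When the patient attends the clinic |
| Registry health care use | Yes | Yes | When care is used |

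The Data collection section confirms the fixed schedule: "Measurements will be repeated 4 times during the 22 months". Between baseline and 16 weeks there is no trial visit for symptom scales. A complaint that arises and resolves in that window, without a clinic or other health care contact, can leave no trace in the rows shared by both arms.

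**2. What the shared measures can show.** For a symptom scale with 75 per arm, before any gain from baseline adjustment:
- 95% CI half-width = 1.96 × √(2/75) = 0.32 SD.
- Difference detectable with 80% power = (1.96 + 0.84) × √(2/75) = 0.46 SD.

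A moderate average worsening of pain, fatigue or function against controls is therefore detectable.

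**3. What the one-arm report can show.** The plan states no side-effect rate, so the rates here are assumptions. Suppose 30% of intervention patients report a joint complaint. The excess due to the programme is 30% minus the unmeasured background rate:
- background 10%: excess 20 points;
- background 20%: excess 10 points;
- background 30%: excess 0.

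The same observed 30% fits all three, and the plan collects nothing from this instrument to choose between them.

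**4. What asking both arms would give.** For a risk difference with 75 per arm and equal rates p, half-width = 1.96 × √(2p(1−p)/75):
- p = 0.20: 1.96 × √(0.32/75) = 0.128;
- p = 0.30: 1.96 × √(0.42/75) = 0.147.

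That is about 13 to 15 percentage points if all 150 answer. Over assumed control rates of 10% to 50%, power is about 69% to 87% for a 20-point excess and 23% to 40% for a 10-point excess.

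**5. The plan's own sample size.** It is not at issue, but it reproduces. With a difference of 50 minutes, SD 102 and two-sided 0.05, the pooled t-test gives 80.4% power at 67 per group and 84.7% at 75.

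**The case against.** **The trial does measure RA symptoms in both arms.** This stands. A reader might infer that the trial cannot tell harm from ordinary RA symptoms at all. The documents do not support that: Table 1 schedules symptom scales, disease activity and painkiller use for everyone, DANBIO and registry data cover both arms, and Statistical analysis compares the arms by intention to treat. Only event-type complaints that these sources can miss remain uncovered. Group means can also hide a harmed minority.

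**The questionnaire is not limited to completers.** This also stands. A reader might take the timing phrase to mean that only those who finished are asked. The sentence says all intervention participants; the phrase fixes when, not who. It does leave open how patients who stop counseling early are reached, which is worth making explicit.

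**It is a process evaluation, not a safety endpoint.** This is fair in part. No objective or outcome presents it as a comparative safety rate, and its process, quality and impact items cannot sensibly go to controls. But side-effects are named among its contents, and that part can be asked of anyone if worded as events.

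**A condensed article leaves adverse-event procedures to the full protocol.** This is true, and a missing fuller plan is no finding. Table 1 is also not exhaustive: it omits this questionnaire and hip circumference. The point rests instead on a stated rule about who is asked and when.

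**The remedy is imprecise and self-reported.** This is correct. It would detect only sizeable excesses, and unblinded patients may still report differently. It nevertheless gives a between-arm estimate where the present rule gives none.

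**Conclusion.** The point holds in a limited form. Side-effect reports come from one arm, once, and cannot be compared with a background rate. The gap is confined to falls, injuries, transient flares and local joint complaints that the shared measures and health care records can miss.

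The plan's between-arm information from this instrument is nil. The available alternative is a risk difference with a half-width of about 13 to 15 points, assuming rates of 20 to 30% and answers from all 75 per arm. The conclusion about the missing comparator does not depend on those rates; only the precision does.

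Severity is minor and this is a cheap improvement. The primary outcome, sample size and planned efficacy analyses are untouched.

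**What to change.** Split the end-of-programme questionnaire in two.

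- Keep the process, quality and impact items for the intervention arm.
- Put the side-effect items to all 150 randomized patients on the tablet at the existing 16-week assessment. Word them as events without reference to the programme, for example new or worsened joint complaints, falls, and injuries in the past 16 weeks.
- State that patients who stopped counseling early are asked as well.
- Report the risk difference with its 95% CI, which Statistical analysis already provides for dichotomous outcomes.

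The cost is a few extra items for 75 control patients, with no new visit or staff. Remaining limits are reporting bias from unblinded patients and modest precision, so an interval that includes zero should not be read as evidence of safety.

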#### Control group

The control group will be encouraged to maintain their usual lifestyle during the 16-week intervention period. When the last follow-up examination is completed they will be offered the opportunity to join an information session (in groups) about the principles of the intervention.

### Primary outcome measure

Change in total daily sitting time in minutes [41,42] from baseline to 16 weeks.

#### Changes in objectively measured sitting time

Measurements will be obtained using an ActivPAL® 3 TM Activity Monitor (PAL Technologies, Glasgow, UK). This is a small (2.0 × 1.4 × 0.3 inches) and light (20.1 grams) uniaxial accelerometer-based device [43] that is worn anteriorly on the upper right thigh and kept in place by waterproof dressing and adhesive tape. The monitor registers total physical activity level over a 7-day period. The monitor uses accelerometer-derived information about thigh position to estimate time spent in different body positions (that are sitting/lying, standing and walking; sleeping time will be deducted from data). Data will be processed as 0.1 second events data using the ActivPAL® software (version 6.4.1; PAL Technologies, Glasgow, UK). The ActivPAL® monitor has previously been validated against direct observation and compared with the Actigraph® GT3X Activity Monitor accelerometer (Pensacola, FL, USA) [42,44]. It is currently considered the best choice for objective measurement of sitting/lying. The ActivPAL® has also been found sensitive to change in sitting time [44].

### Secondary outcome measures

#### Changes in self-reported sitting time

Changes in self-reported daily sitting time at work and during leisure time will be measured by the Physical Activity Scale 2.1 (PAS 2.1) [34], a modified version of the original PAS questionnaire, which has previously been validated against accelerometer, physical activity logs and maximum oxygen uptake [45,46]. Respondents will be asked to specify number of hours and minutes in an average 24-hour day spent sitting at work and during leisure time.

##### Fatigue

The 20-item Multi-dimensional Fatigue Inventory (MFI 20) [47] will be included to measure fatigue. MFI 20 consists of 20 statements such as ‘I feel enthusiastic’ and classifies fatigue in five dimensions: 1) general fatigue 2) physical fatigue 3) mental fatigue 4) reduced activity 5) reduced motivation.

##### Pain

The Visual Analogue Scale (VAS) [48] transforms the subjective experience of pain to a measurable quantity. The participant indicates his or her pain by putting a mark on the line where the ends are marked with ‘no pain’ to ‘worst imaginable pain’. VAS is included in the HAQ (see below).

##### Physical function

Health Assessment Questionnaire (HAQ) [35] is an instrument that contains twenty items with four possible answers in eight categories of functions within the ADL (regular daily activities): dressing, rising from a seat, eating, walking, personal hygiene, stretching for an object, grabbing objects and everyday activities. In addition, the HAQ includes VAS scales pain, fatigue and general health.

##### Health-related quality of life (HR-QoL)

HR-QoL is assessed with: 1) SF-36 (The Short Form [36] Health Survey) [49] which will be included to measure QoL, which is a generic instrument consisting of 36 items divided into 8 scales: physical function, physical activity limitations, pain, general health, vitality, social function, emotional activity limitations and mental health [49]; 2) EuroQol (EQ-5D-5 L) is a standardized 5-item instrument developed to provide a simple, generic measure of HR-QoL for clinical and economic appraisal [50]. The EQ-5D-5 L descriptive system comprises the following 5 dimensions: mobility, self-care, usual activities, pain/discomfort and anxiety/depression. Each dimension has five levels: no problems, slight problems, moderate problems, severe problems and extreme problems. The responses can be scored into a single utility index based on Danish preference data [51].

##### Self-efficacy

The General Self-Efficacy Scale (GSES) [52] assesses a general sense of perceived self-efficacy with the aim of predicting coping with daily hassles and adaptation after experiencing stressful life events. The instrument is a 10-item scale with statements such as ‘I can usually handle whatever comes my way’ and ‘I am confident that I could deal efficiently with unexpected events’. The response format is ’not at all true’, ‘hardly true’, ‘moderately true’, ‘exactly true’. The instrument is translated and validated in a Danish context.

##### Additional questions on sedentary behavior

Additional questions on duration of sitting time and interruptions in sitting time on weekdays and in weekends are included. The questions have been validated against Actigraph (Pensacola, FL, USA) accelerometers in a recent Danish Study [53].

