### Self-administered retrospective questionnaire

At termination of the objective diurnal measurements, a self-administered questionnaire is applied regarding specific recall of time sitting during the measurement period. Time spent sitting during working hours is obtained by the question: ‘during working hours in the measuring period, in average per day, how long time did you spent sitting?’ [5-7,11] reported in hours and minutes. The longest continuous time with uninterrupted sitting is obtained from the question: ‘during working hours in the measuring period, how long is the longest uninterrupted time you have spent sitting?’ reported in hours and minutes. Both questions are also asked for leisure time before/after a workday and leisure time on a complete leisure day [7,11]. The questions used in this study are inspired both by International Physical Activity Questionnaire (IPAQ) [11] and Medical Outcomes Study Patient Assessment Questionnaire MOSPAQ [5,24] (modified Occupational Physical Activity Questionnaire (OPAQ) to specially measure sitting time) together with the new possibilities of the improved objective measurements, that allow specific measurement of sitting during work and leisure time.

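### Sitting interruptions and longest sitting bout, which the intervention coaches directly, are measured only by unblinded self-report, although the monitor data could supply them objectively

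*Protocol article*

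**What the plan says.** **What is coached.** In Contents of motivational counseling, the last two of the four key messages are "3) break up prolonged sitting - by standing up frequently and 4) maximum 30 minutes of sitting per episode". The catalogue of ideas used for goal setting is one "which contains proposals to reduce and create breaks in sitting time", so breaks are a goal alongside less sitting overall.

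**How the pattern is measured.** Under Secondary outcome measures, the subsection Additional questions on sedentary behavior states: "Additional questions on duration of sitting time and interruptions in sitting time on weekdays and in weekends are included". It adds: "The questions have been validated against Actigraph (Pensacola, FL, USA) accelerometers in a recent Danish Study". The section Self-administered retrospective questionnaire says: "At termination of the objective diurnal measurements, a self-administered questionnaire is applied regarding specific recall of time sitting during the measurement period". In that questionnaire, "The longest continuous time with uninterrupted sitting is obtained from the question", put separately for working hours, leisure around a workday, and full leisure days.

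**What the monitor is used for.** The primary outcome is "Change in total daily sitting time in minutes" from baseline to 16 weeks. Table 1 has one monitor row, total sitting time, at baseline and the three later assessments. Changes in objectively measured sitting time says the device distinguishes sitting or lying, standing and walking, and "Data will be processed as 0.1 second events data using the ActivPAL® software". Data collection adds round-the-clock wear for 7 days and a diary to separate sleep from sitting.

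**Blinding.** Randomization and blinding states that patients are not blinded; only the assessors are.

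**The concern.** A self-completed answer is not protected by a blinded assessor. Both arms know their allocation, but only one is taught the 30-minute ceiling and is later asked how long its longest sitting was. Any tendency to answer in line with the coaching falls on one side of the comparison. It would appear as more interruptions, or a shorter longest bout, than actually occurred.

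What is at stake is the evidence on two of the four coached behaviours. If patients break up their sitting but total minutes fall only modestly, the primary outcome may show little, and the planned evidence on the pattern would be the kind most open to reporting bias. An objective record exists in files the trial already collects. If it is used only after the results are known, it loses the standing of a prespecified analysis.

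**Working it through.** **1. The plan's own figure.** Inputs from Feasibility study and power calculation: difference 50 minutes, SD 102 minutes, two-sided alpha 0.05; 1:1 allocation from Trial design. For a pooled t-test the noncentrality is difference / (SD × √(2/n)), with 2n − 2 degrees of freedom.
- n = 66 per group: power 79.8%
- n = 67 per group: power 80.4%
- n = 75 per group: power 84.7%

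The stated 67 per group and 84.7% both reproduce. The sample size is not in dispute.

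**2. Measure against target.**

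| Coached behaviour | Measure named | Source |
|---|---|---|
| Less sitting overall | Total daily sitting time | Monitor (primary outcome); self-report on the Physical Activity Scale (secondary) |
| Frequent interruption | Additional questions | Self-report |
| At most 30 minutes per episode | Longest unbroken sitting | Self-report |

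The article does not say in words that the monitor yields breaks and bouts. It follows from event-level posture data: the start and end of each sitting event give the number of transitions and the length of every bout, and the sleep diary allows restriction to waking time. The recall items on longest sitting refer to the monitor week itself. The additional questions on interruptions are not tied to that week, but Table 1 schedules the sedentary-behaviour questions at the same four time points as the monitor.

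**3. How far total minutes respond to the two messages.** Assume 10 hours of sitting a day (the feasibility mean was 10.13 hours) in 60-minute bouts: 600 / 60 = 10 bouts. Add one break of L minutes at the middle of each, taken out of sitting time. The article gives no break length, so L is varied.

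| L (min) | Fall in sitting, 10 × L | Share of 50 min | Each remaining bout, (60 − L)/2 | Minutes in bouts over 30 |
|---|---|---|---|---|
| 1 | 10 | 20% | 29.5 | 600 → 0 |
| 2 | 20 | 40% | 29 | 600 → 0 |
| 5 | 50 | 100% | 27.5 | 600 → 0 |

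The pattern measure changes completely in every row. The total changes by one fifth to all of the planned difference.

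If a 20-minute fall were the whole group difference, power with 75 per group and SD 102 would be 22%. The ANCOVA reduces the SD to 102 × √(1 − r²). For an assumed baseline correlation r of 0.5 (SD 88.3) or 0.7 (SD 72.8), power is 28% or 39%.

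**4. What a reporting shift would do.** The documents give no size for this bias, so it is assumed, in SD units of a self-report item. With no true effect and 75 per group, the chance of p < 0.05 is:
- shift 0.1 SD: 9%
- shift 0.2 SD: 23%
- shift 0.3 SD: 45%
- shift 0.5 SD: 86%

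Without bias it is 5%. These figures show sensitivity and do not estimate the bias in this trial.

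**The case against.** **This is only an omission.** The article condenses a fuller protocol and refers to a pre-established analysis plan, which may derive more variables from the monitor; nothing says it will not. That is fair as far as it goes. But the article is not silent on sitting pattern: it assigns interruptions and longest sitting to questionnaires, with wording and recall period for the latter, while naming total time alone for the monitor. That is a stated choice of measure and can be reviewed as one.

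**The questions are validated.** The article says so for the additional questions, and it should be acknowledged. Agreement with an accelerometer in another study does not show that coached and uncoached patients who know their arm report alike.

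**Sitting pattern is not a declared objective.** This stands. The Objectives concern total sitting time and its relation to health outcomes, and no stated hypothesis rests on interruptions. It limits the severity.

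**The illustration is artificial.** This also stands in part. Break length is assumed, and messages 1 and 2 act directly on total minutes within the same package.

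**Stronger readings that the text does not support.** A reader might infer that the primary endpoint barely moves when messages 3 and 4 are followed; the falls of 10 to 50 minutes contradict that. A reader might also infer that the trial cannot tell whether lost sitting became standing or walking. The monitor estimates both; they are simply not named as outcomes. Nor would naming new secondary outcomes rescue a null primary result, since the primary outcome stays total minutes.

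**The recall items have a separate use.** They split work from leisure, which is a reason to keep them.

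**Conclusion.** The point holds as a minor one. Interruptions and longest unbroken sitting are coached in one arm and measured only by self-report from unblinded patients, although event-level monitor data from the same four time points can give them objectively, and over the same week for the longest-bout items. Self-reported pattern results could therefore show an effect that is only reporting.

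Its size cannot be derived from the documents. The false-positive figures rest on assumed reporting shifts, and the 10, 20 and 50 minutes on assumed break lengths and 10 breaks a day. The conclusion itself rests on neither; it follows from who is coached, who is blinded, and which instrument is named for which behaviour.

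The primary outcome, sample size and declared objectives are unaffected. No primary conclusion changes.

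**What to change.** Name a short set of monitor-derived secondary outcomes for sitting pattern, in the outcome section and in Table 1:
- sit-to-stand transitions per day
- minutes per day in waking sitting bouts longer than 30 minutes
- longest waking sitting bout
- standing minutes and walking minutes per day

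Analyse each with the ANCOVA already planned (factor for group, baseline value as covariate). State that the questionnaire items on interruptions and longest sitting are supportive, and keep them for the split between work and leisure.

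The cost is some extra processing of files already collected and a few lines of text, with no new visits, devices or patient burden. The one drawback is a few more secondary comparisons in a plan that does not adjust for multiplicity, so the list should stay short and be fixed before unblinded data are examined.
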